##### Electroencephalography (EEG) Data

EEG can be used as an outcome predictor for the intervention, or prospectively in order to determine the chance of progressing towards MCI or other Dementia-like state (Poil et al., 2013). Moreover, EEG can be used to assess changes in brain connectivity in people with MCI (Tóth et al., 2014).

### Trial Design, Setting, and Registration

The trial will be an exploratory three arm parallel group, double blinded controlled trial, with an 1:1 allocation (see Figure 1). Data will be collected from clinical outpatient services from the Northern and Center Regions of Portugal. This trial has been registered at Clinicaltrials.gov with the identifier: NCT05198726.

**Figure 1 F1:**
[figure not shown]
Schematic representation of the protocol.

Participants will perform a pre-screening procedure in order to assess their eligibility for the study. If they are eligible, they will be screened by a trained clinician (neurologist or neuropsychologist) in order to assess if there is evidence of modest cognitive decline from a previous level of performance; that these deficits do not impair participant’s independence; that the cognitive decline is not a result of a delirium, or better explained by other mental disorder such as depression or schizophrenia as suggested by DSM-V (American Psychiatric Association, 2013). Participants that screen in, will perform a baseline assessment, which will consist of the UFOV, the NIH EXAMINER, and the EEG data. Then they will perform an intervention that will last for 15 sessions. For the first 3 weeks, participants will receive nine sessions of the intervention, and then will receive two sessions per week (i.e., booster) for the following 3 weeks. We will then conduct three follow-up assessments at 1, 3, and 6 months after the stimulation has ended. Assessments will be similar across all study points.

### Participants

Participants will be community-dwelling adults aged 65 years and older, with cognitive complains in memory or other functions, which have declined over time. Participants will be excluded if they are less than 65, score in the mini mental examination less than 23 (or over 28), diagnosis of Alzheimer’s Disease, any other medical condition that may predispose participants for a forthcoming decline in function, or that may increase their risk of mortality during the duration of the study. Participants will also be excluded if they have any contra-indication to tACS, severe sensory losses or communication difficulties that will prevent them from successfully complete the training or had any cognitive training in the past.

Voluntary and written informed consent will be obtained from the participants by a researcher, which will explain in detail the procedures involved in the study.

### Description of the Interventions

#### Speed of Processing (SoP)

There will be a total of 15 sessions (30-min per session) of SoP training. These sessions will be performed three times a week for the first 3 weeks and two times a week for the following 3 weeks, and will consist of four conditions. In condition 1, participants will be asked to identify objects at increasingly brief exposures (see Figure 2A). For condition 2, identification of stimulus on the center of the screen will be requested from participants, while a second stimulus will appear somewhere in peripheral vision—stimulus duration, difficulty of the central localization task or the area in which targets may be located, will be used to change the level of difficulty (see Figure 2B). Condition 3 is similar to condition 2, but visual distractors are added. Finally, for condition 4, an auditory identification component will be superimposed over the visual task (Jobe et al., 2001).

**Figure 2 F2:**
[figure not shown]
Schematic representation of the two first conditions of the Speed of Processing (SoP) task. Panel **(A)** represents condition 1, with only one target. Panel **(B)** represents condition 2, in which a second target is added (i.e., diamond).

Objects time exposure will decrease by 50 ms if in the preceding block of 20 trials, participants successfully recognized the object in at least 75% of trials. If not, time exposure of objects will go up by 50 ms. Once exposure of objects cannot be reduced for three consecutive blocks of 20 trials, participants may proceed to the next condition. Visual targets will be approximately 2 cm in wide and height, which represents a visual angle of 1.9° at a 60 cm distance. For the sham version of the task, objects time exposure will be fixed across all trials (i.e., 500 ms).

#### Endogenous Alpha-Transcranial Alternating Current Stimulation (α-tACS)

Participants will do a run-in phase (EEG without α-tACS) during the first 5-min of each training session in order to trace the individual alpha frequency (IAF) over occipital regions (defined as the maximum alpha value within the 7–13 Hz range), which will then be used to deliver the 2 mA α-tACS (based on the IAF) over the prefrontal cortex (PFC; i.e., F3 and F4) for 20-min, using 35 cm^2^ sponges. The PFC was chosen due to his age-related decline (Fjell et al., 2013) and to his involvement in visual target processing (Madden et al., 2004). For the sham tACS, a 45-s of active α-tACS will be applied. This will allow to mimic the initial sensation of tACS. The computer screen will randomly flicker across the experiment for the sham tACS, because active tACS bellow 40 Hz is likely accompanied by visual flicker sensations. Thus, we plan to use the computer screen to mimic this flickering for the sham tACS condition. In order to continuously monitor electroencephalographic (EEG) activity and deliver α-tACS during task performance, a custom Loop-IT solution from Neurocare (Germany) will be used.

### Outcomes

Main outcome will be the Useful Field of View (UFOV) test for speed of processing and attention (Ball et al., 1988). The UFOV is a test that was designed to evaluate daily life difficulties experienced by the elderly, such tasks that require divided visual attention and have to be undertaken rapidly (speed of processing). The four-subtest stimulus will be used for the computerized version, namely identification alone; divided attention; selective attention; selective attention in conjunction with same/different discriminations will be used (Edwards et al., 2006). UFOV is expected to be completed in 10 min and participants are asked to touch the screen as soon as they identify a target (i.e., a car silhouette inside a box), with the target exposure ranging from 16.67 to 500 ms. In order to probe divided attention, a peripheral target is added to the central target. For the selective attention, distractors are added; while for the more demanding version, there are two central targets, and participant are asked to make a judgment if they are similar or not.

The NIH EXAMINER battery will be used for assessing transfer effects of the intervention to untrained domains. The NIH EXAMINER comprises cognitive control, verbal fluency, and working memory assessments (Possin et al., 2013). Namely, NIH EXAMINER is a computerized version of several tasks targeting working memory, inhibition, set shifting, fluency, insight, planning, social cognition, and behavior, which allows for the calculation of a composite score (Kramer et al., 2014). As the time to complete several tasks is performance dependent, we expect participants to complete the NIH EXAMINER between 30 and 60 min.

Resting state EEG will be used as a surrogate outcome, and will be performed before and immediately after the intervention in order to assess power spectral density changes, cross frequency couplings and coherence among electrodes. Participants will also perform a short auditory oddball task (Fz, Cz, Pz, and Oz) because the P3 wave is a good marker of brain’s speed of processing. Analysis will be considered exploratory if the dropout rate reaches 20%.

At week 3 and 6 outcomes will be collected the following business day, due to particular characteristics of the sample.

### Sample Size

No previous studies using tACS and SoP have used UFOV as a primary outcome, and as such, we are using the UFOV test-retest data from Bentley et al. (2012). For older adults the mean (SD) test-retest difference (i.e., consistency between measurements at two different timepoints on the same sample) between UFOV applications was 56.2 (74.8). In order to show an effect, our intervention should at least surpass the mean test-retest difference. So we ran three different scenarios: 0.50, 0.75, and 1.00 SD below mean difference for older adults, with a power of 0.8 and alpha of 0.05. In these scenarios, a minimum of 17 participants and a maximum of 64 per group would be required in order to detect a Cohen’s d of 1 and 0.5, respectively. However, these values were above the mean test-retest difference for younger adults, namely 31.5 (43.7). As such we used this value as our cut off point, and with a power of 0.8 and alpha of 0.05 we would need at least 98 participants per group. If an attrition rate of 10% is considered, 109 participants per group will be required. However, having trial feasibility into consideration, we decided to conduct a interim analysis for futility as soon as 19 participants per group are reached, then at 32 participants per group and finally at 71 participants per group (always considering the 10% attrition rate).

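### The 98 per group is reproduced by pooling in the younger adults' SD; with the older-adult SD that the plan quotes, power for the implied 24.7-point difference is about 63%, not 80%

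*Protocol article*

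**What the plan says.** All the sizing figures are in the protocol article, Methods, Sample Size.

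- For older adults, the mean (SD) test-retest difference "between UFOV applications was 56.2 (74.8").
- Three scenarios of 0.50, 0.75 and 1.00 SD are considered. The plan reports "a minimum of 17 participants and a maximum of 64 per group would be required in order to detect a Cohen’s d of 1 and" (the second effect being d = 0.5).
- It then says that "these values were above the mean test-retest difference for younger adults, namely 31.5 (43.7").
- It continues: "As such we used this value as our cut off point, and with a power of 0.8 and alpha of 0.05 we would need". The number it then gives is a minimum of 98 in each group. Allowing 10% attrition, this becomes 109 per group, which over three arms is the 327 in the Abstract.
- It also plans to "conduct a interim analysis for futility as soon as 19 participants per group are reached", then at 32 and at 71.

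The Participants section describes those enrolled as "community-dwelling adults aged 65 years and older". The target difference, the SD, Cohen's d and the sidedness behind the 98 are not stated.

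**The concern.** The 98 is the figure from which 109 and 327 follow, and its only justification is the claim of 80% power. Two means and two SDs are printed, and the reader is not told which enter the calculation. If the younger adults' SD was used, the outcome is assumed to vary less than the plan's own older-adult data show, in a trial that enrols no younger adults. The stated power is then too high, and a non-significant result would carry less information than an 80%-powered trial implies.

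The interim looks come from the same paragraph but from larger effects than the one that sets the final size. How a non-significant look should be read therefore needs care.

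**Working it through.** **Inputs (Sample Size):** older adults 56.2 (SD 74.8); younger adults 31.5 (SD 43.7); power 0.80; alpha 0.05; attrition 10%. **From Participants:** all aged 65 or older.

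**Step 1: identify the method.** A two-sample, two-sided t test at 80% power needs 16.7, so 17 per group, for d = 1, and 63.8, so 64 per group, for d = 0.5. Both match the plan. For d = 0.75 it gives 28.9, so 29.

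**Step 2: reproduce the 98.**
- Difference: 56.2 - 31.5 = 24.7.
- SD: sqrt((74.8² + 43.7²)/2) = sqrt(3752.4) = 61.26.
- d = 24.7/61.26 = 0.403.
- n = 97.5, so 98 per group.
- 98/0.9 = 108.9, so 109; 3 × 109 = 327.

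The whole chain agrees with the plan. Other combinations, two-sided at 80% power unless noted:

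| Difference | SD | n per group |
|---|---|---|
| 24.7 | 61.26 (root mean square) | **98** |
| 24.7 | 59.25 (simple mean of SDs) | 92 |
| 24.7 | 74.8 (older) | 145 |
| 24.7 | 74.8, one-sided | 115 |
| 24.7 | 43.7 (younger) | 51 |
| 31.5 | 74.8 | 90 |
| 31.5 | 61.26 | 61 |
| 31.5 | 43.7 | 32 |

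A three-group F test on 24.7 and 61.26 gives 90 or 120, depending on the pattern of means. A bare d rounded to 0.40 gives 100 by the t test. That is close, but the text does not state it.

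**Step 3: use the older-adult SD.**
- d = 24.7/74.8 = 0.330.
- Power at 98 per group: 63.3% (normal approximation 63.7%).
- n for 80%: 144.9, so 145 per group. With attrition, 145/0.9 = 161.1, so 162 per group and 486 in total.
- Detectable at 80% with 98 per group: d = 0.4022, and 0.4022 × 74.8 = 30.1 points.

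**Step 4: the alternative target.** If 31.5 is itself the difference to detect, d = 31.5/74.8 = 0.421 and power at 98 is 83.5%.

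**Step 5: the sentence about 31.5.** As differences to detect at SD 74.8, the scenarios are 0.50 × 74.8 = 37.4, 0.75 × 74.8 = 56.1 and 1.00 × 74.8 = 74.8. All exceed 31.5. As values subtracted from the mean they are 56.2 - 37.4 = 18.8, 56.2 - 56.1 = 0.1 and 56.2 - 74.8 = -18.6. None exceeds 31.5.

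**Step 6: the interim looks.** 17/0.9 = 18.9, 29/0.9 = 32.2 and 64/0.9 = 71.1, which round to 19, 32 and 71. The looks are therefore the attrition-inflated sizes for d = 1.0, 0.75 and 0.5. At d = 0.403, power with 17, 29 and 64 evaluable per group is 0.21, 0.33 and 0.62.

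**The case against.** The strongest objection is that 24.7 is inferred. The only number the plan calls its cut-off is 31.5. Read literally as the difference to detect, with SD 74.8, it leaves no shortfall: power is about 83%, and the 30.1 points detectable at 80% lie below 31.5. This stands as a limit on the claim. A reader might infer that the trial's power simply is 63%, and the document does not support that without the condition on the target. But the 31.5 reading needs 90 per group and does not explain the printed 98, whereas the pooled-SD reading does so exactly.

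A reader might also infer that the sentence placing the scenarios above 31.5 is false. It is true if the scenarios are differences of 37.4 to 74.8 points, and the plan does express them as Cohen's d. The wording is unclear, not shown to be wrong.

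A third tempting inference is that the interim looks will cost much power or inflate type I error. That requires stopping rules or efficacy claims that the article does not contain. It says only that the looks are for futility, and boundaries may properly sit in the full protocol or SAP. Under a rule based on conditional power below 20% at the planned difference, simulated power is about 0.80 with all three looks or with the look at 71 alone.

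Finally, the trial is described as exploratory. That softens the consequence, but the plan still names primary and co-primary endpoints and justifies its size by a power figure.

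**Conclusion.** The point holds in conditional form. The plan does not state the difference or SD behind 98. The one combination found to reproduce it borrows an SD from a population the trial does not enrol. On that target of 24.7 points, with the plan's own older-adult SD, power at 98 evaluable per group is about 63% and 80% needs 145. On a target of 31.5 points, power is about 83%, but 98 is then unexplained. Either way, the stated number and its inputs need to be reconciled.

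This rests on a two-sided, two-group t test, as the 17 and 64 imply, and on SD 74.8 carrying over to the trial's participants. A one-sided test would give about 74% for 24.7 points, and having all 109 per group evaluable would give 68% two-sided; both stay below 80%.

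On the interim looks, the documents support only this: they are timed for larger effects than the one behind 98, so non-significance there says little about futility. They do not show that the looks harm the trial.

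**What to change.** Keep 98, 109 and 327. In Sample Size:

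1. State the target difference in UFOV points, the SD of 74.8 and the two-sided test.
2. Restate the power: 98 evaluable per group with SD 74.8 gives 80% for about 30.1 points (d = 0.40) and 63% for 24.7.
3. Reword the comparison with 31.5 to say that the scenarios are differences of 37.4, 56.1 and 74.8 points.
4. Add that 19, 32 and 71 are the inflated sizes for d = 1.0, 0.75 and 0.5, that power there at d = 0.40 is 0.21, 0.33 and 0.62, and that a non-significant result at a look is not in itself futility. Dropping the first two looks is optional.

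The cost is a few sentences and a less favourable stated power. No extra participants are needed.

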### Recruitment

Recruitment will be made in the north and center regions of Portugal, using broad community advertisement strategies (i.e., Facebook page, flyers) and by targeting specific organizations that usually work with the elderly such as senior universities and assisted care home facilities.

### Randomization

Participants will be block randomized (random block sizes of 2, 4 or 6) by a computerized software to one of the interventions. Allocation concealment will be kept using a method of closed envelops, which will only designate Group A or B. A or B will then be used to set up a masked study mode on the device. Randomization list will be kept on a secured storage, and the access will be restricted to the Principal Investigator. Enrolment of participants will be performed by a researcher of the trial, and the allocation will be performed immediately prior to the beginning of the stimulation sessions.

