### Blinding Procedures

This will be a double blind design, in which trial participants, researchers providing the interventions and outcome assessors will be blinded to the intervention. This will be achieved using study mode of the devices and employing sham procedures for the α-tACS. Participants will be unblinded if they experience any unexpected adverse effects. At the end of their participation, blinding assessment will be performed to both participants and researchers who assessed the outcomes, namely by asking about the stimulation that they thought they had received (or applied) and to rate how confident they are in their guesses.

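### The Randomization section describes a two-group scheme (envelopes A or B, blocks of 2, 4 or 6) that does not fit the stated three equal arms

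*Protocol article*

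**What the plan says.** The section on trial design, setting and registration calls the study an "exploratory three arm parallel group, double blinded controlled trial, with an 1:1 allocation". The rest of the article agrees on three arms. The Abstract and the primary-outcome analysis compare the combination with each intervention alone, the Discussion says that there is no placebo-only group, and the planned total of 327 is three times the 109 per group in the Sample Size section.

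The Randomization section reads differently: "Participants will be block randomized (random block sizes of 2, 4 or 6) by a computerized software to one of the interventions". It continues: "Allocation concealment will be kept using a method of closed envelops, which will only designate Group A or B". The letter has one stated use: "A or B will then be used to set up a masked study mode on the device".

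SoP training also has two versions: "For the sham version of the task, objects time exposure will be fixed across all trials (i.e., 500 ms". The Randomization section does not say how a participant is assigned to one or the other. The Blinding Procedures section names the device study mode and the sham tACS procedure, but not the SoP version. It also says: "Participants will be unblinded if they experience any unexpected adverse effects".

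**The concern.** The allocation rule is the one part of the method on which every comparison depends, and as written it fits a trial with two groups. A list built literally from that section cannot deliver three equal arms. Whoever builds the list must add something the article does not state: a third code, a 2:1 ratio for the device mode, or a separate rule for the SoP version.

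The choice matters. Some ways of filling the gap cost almost nothing. Others change the arm sizes enough to weaken half of the primary hypothesis, or leave the SoP assignment without a described concealment step.

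**Working it through.** **Inputs.** Three arms, equal allocation (trial design section). Blocks of 2, 4 or 6 and codes A or B (Randomization). Power 0.8, alpha 0.05, 98 per group, 109 after 10% attrition (Sample Size). Total 327 (Abstract). Two-sided testing is assumed, since sidedness is not stated.

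**1. The plan's own figure.** The article does not spell out the step to 98, but it can be reproduced from the two test-retest results in Sample Size. This route is inferred.
- Difference: 56.2 − 31.5 = 24.7
- Pooled SD: √((74.8² + 43.7²)/2) = 61.26
- d = 24.7/61.26 = 0.403
- The two-sample t-test gives 97.5, so 98 per group
- 98/0.9 = 108.9, so 109 per group, and 3 × 109 = 327

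The sample size is consistent with three equal arms and is not in dispute.

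**2. Block sizes.** The remainders on division by 3 are 2 for a block of 2, 1 for a block of 4, and 0 for a block of 6. Only the block of 6 can hold three arms equally (two each). If the three sizes are drawn equally often (an assumption, since no weights are given), blocks of 2 and 4 hold (2 + 4)/(2 + 4 + 6) = 50% of participants.

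**3. What the block sizes cost by themselves.** In 5,000 simulated lists of 327, each block was filled as evenly as possible over three arms. The gap between the largest and smallest arm had median 7 and 95th percentile 14, and exactly 109/109/109 occurred in about 2% of lists. A 14-participant gap such as 102 against 116 leaves pairwise power at 0.80 after 10% attrition.

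**4. Codes.** Two letters separate at most two groups, and 327/2 = 163.5 is not 109.

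**5. If A/B means active or sham tACS.** Two of the three arms receive active tACS. Equal arms therefore need 218 active and 109 sham, a ratio of 2:1. Suppose instead that the list ran 1:1 and the active half was split evenly between real and sham SoP:
- SoP with sham tACS: 327/2 = 163.5
- Combination: 327/4 = 81.75
- tACS alone: 327/4 = 81.75

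Evaluable participants total 3 × 98 = 294, giving 147, 73.5 and 73.5. With d = 0.402, the effect detectable with 98 per group:

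| Comparison | Evaluable n | Power |
|---|---|---|
| As planned | 98 v 98 | 0.80 |
| Combination v SoP alone | 73.5 v 147 | 0.80 |
| Combination v tACS alone | 73.5 v 73.5 | 0.68 |

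A normal approximation agrees for the last row: 0.402 × √(73.5/2) − 1.96 = 0.48, and Φ(0.48) = 0.68. The comparison with SoP alone keeps its power because 73.5 × 147/220.5 = 49 = 98/2.

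**The case against.** Much can be said for the plan. The letter sets the device, and the device has two modes, so A and B plausibly code only the tACS condition. On that reading every participant has an envelope. A reader might infer that one arm of 109 has none, but that follows only if the letters are taken as arm labels.

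Even block sizes do not force active to sham at 1:1, because a block of 6 can be filled 4:2. The 163/82/82 outcome therefore needs two further assumptions: a 1:1 device list and an even split of its active half.

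A reader might also infer that the SoP version is assigned outside the concealed list. The article does not say so. The software randomises to one of the interventions and the list is held under restricted access, which is compatible with a list covering both components. A condensed article may leave the delivery step to the full protocol. Selection bias is possible, not shown.

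Likewise, unblinding one participant need not reveal the allocation of everyone with the same letter. That requires the letter's meaning to be fixed throughout, and the result to reach blinded staff who know other participants' letters. The article states neither.

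These points stand and limit the consequences. They do not remove the contradiction: the article gives no third code, no 2:1 ratio and no rule for the SoP version, and blocks of 2 and 4 remain incompatible with three equal arms.

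**Conclusion.** The trial design and Randomization sections contradict each other, and the allocation rule cannot be carried out as written for three equal arms. This is an internal inconsistency, possibly two-group wording left in a three-arm text.

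Its size depends on how the gap is filled. Non-divisible blocks alone lose exact balance (a gap of about 7, seldom above 14, among 327) with almost no loss of power and no bias by themselves. A 1:1 device list with its active half split evenly would lower power for the combination against tACS alone from 80% to about 68%. That rests on d of about 0.40, 10% attrition and two-sided testing. Selection bias in the SoP assignment and wider unblinding through shared letters are risks to close off, not established faults.

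The text must be corrected because allocation underlies every comparison.

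**What to change.** Reconcile the two sections as follows:
- State 1:1:1 allocation over three arms, generated from one concealed list.
- Use block sizes that are multiples of 3, for example 3, 6 and 9 in random order. Each complete block is then exactly balanced, and 109 per arm is reachable.
- Replace the shared letters with participant-specific masked codes, each setting both the tACS mode and the SoP version. This also removes the route by which one unblinding could inform on others.

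The sample size stays at 98 evaluable and 109 enrolled per group, 327 in total. Before enrolment the cost is a new list, the set-up of the codes and a corrected paragraph. The article does not give enrolment status. If participants have already been allocated, the sponsor should check which list and ratio are in use, report them, and describe any change of list.

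### Small blocks and one pair of letters shared by all participants put allocation concealment at risk if enrolling staff can see past letters

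*Protocol article*

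**What the plan says.** The Randomization section fixes the block sizes: "Participants will be block randomized (random block sizes of 2, 4 or 6) by a computerized software to one of the interventions". It then describes concealment: "Allocation concealment will be kept using a method of closed envelops, which will only designate Group A or B". The letter is also used in the session: "A or B will then be used to set up a masked study mode on the device". One pair of letters thus serves all participants, and whoever sets up the device sees the letter but not its meaning.

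On roles and timing it says "Enrolment of participants will be performed by a researcher of the trial" and that "the allocation will be performed immediately prior to the beginning of the stimulation sessions". Only the principal investigator has access to the list. The section does not say who opens the envelopes, whether the enrolling researcher sees earlier letters, or whether there is one list or one per site.

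Three other places bear on what a letter means:

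- Blinding Procedures provides for unblinding a participant who has an unexpected adverse effect.
- The α-tACS section says "The computer screen will randomly flicker across the experiment for the sham tACS".
- The text on the training task, next to Figure 2, says that in the sham version "objects time exposure will be fixed across all trials", whereas the active version adapts after each block of 20 trials.

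**The concern.** A closed envelope hides the next allocation only if the earlier ones do not give it away. With blocks of 2, 4 or 6, two letters are never far out of balance, so a person who keeps a running count can favour the letter that is behind. Masking what the letter means is the remaining protection. That protection is shared: if A or B is decoded once, it is decoded for all past and future participants.

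If both steps happened, candidates could be brought forward, deferred or encouraged according to the arm expected next. This is selection bias. It would act directly on the comparison of the combination with each single intervention. The planned switch to ANCOVA when baseline differences are significant would not reliably remove it, because selection can work through features that are not measured.

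**Working it through.** The protocol gives no predictability figure, so there is none to reproduce.

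**Inputs.** From Randomization: block sizes 2, 4, 6 and two letters. From Sample Size: 109 per group, so 3 × 109 = 327 allocations. Assumed: one list, all earlier letters known, and the three sizes equally likely. Other size probabilities are tried in step 3.

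**1. Exact check with block sizes known.** The best guess is always the letter with more places left in the block. Expected correct guesses per block:

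- Size 2: 1/2 + 1 = 1.5, and 1.5/2 = 75%.
- Size 4: 1/2 + 2/3 + 2/3 + 1 = 2.833, and 2.833/4 = 70.8%.
- Size 6: 0.5 + 0.6 + 0.6 + 0.7 + 0.7 + 1 = 4.1, and 4.1/6 = 68.3%.

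With equal numbers of blocks: (1.5 + 2.833 + 4.1)/12 = 70.3%.

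**2. Simulation with only the menu of sizes known.** Permuted-block lists of 327 were generated. The guesser updated the probability of each possible block size after every letter.

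- Correct guesses: 70.2%. Simply choosing the letter used less often so far also gives 70.2%, so the menu need not be known.
- Predictable with at least 80% certainty: 52% of allocations. These guesses are right 85% of the time.
- Fully certain: about 4%. No information at all: about 41%.

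**3. Sensitivity to the unstated size probabilities.**

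| Probabilities of sizes 2, 4, 6 | Correct | At least 80% certain |
|---|---|---|
| 0.2, 0.3, 0.5 | 69.5% | 28% |
| 1/3 each | 70.2% | 52% |
| 6/11, 3/11, 2/11 (equal participants per size) | 71.4% | 57% |

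The hit rate is stable. The 80% share is not, because many allocations lie close to that threshold. At 75% certainty the first two rows are much closer, at 53% and 59%.

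**4. What larger blocks would change.**

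| Scheme (sizes equally likely) | Chance | Correct | At least 80% certain |
|---|---|---|---|
| Two letters, 2/4/6 | 50% | 70% | 52% |
| Two letters, 4/6/8 | 50% | 68% | 25% |
| Three arms, 3/6/9 | 33% | 55% | 12% |
| Three arms, 6/9/12 | 33% | 53% | 8% |

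Only rows with the same number of labels should be compared. Dropping the block of 2 halves the highly predictable share but barely moves the hit rate. With three arms, larger blocks gain 2 percentage points in the hit rate (55% to 53%) and 4 in the 80% share (12% to 8%).

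**5. From guess to bias.** Suppose the letters were decoded and every guess acted on. If selection shifts expected outcome by q, the two-arm bias is q(2p − 1), which at p = 0.70 is 0.40q. The documents give nothing from which q could be set, so no bias in SD units is claimed.

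**The case against.** The strongest reply is that the protocol does not say the enrolling researcher opens envelopes, sees past letters or counts them, and that a journal article commonly leaves such role details to the full protocol. This stands. The silence is not itself a fault, and every figure above is conditional on past letters being visible. A reader might infer that concealment fails; the text does not support that.

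Second, what can be guessed is a masked letter, not a treatment, and providers and assessors are stated to be blinded. This also stands as far as it goes. The documents do not say that letters get decoded. They do contain routes by which it could happen, and a shared letter turns one decoding into a decoding for all.

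Third, the 70% and 52% describe two labels, while Trial Design, Setting, and Registration describes three arms. Two letters cannot name three arms, and blocks of 2 or 4 cannot balance them. That contradiction is a separate point and must be reconciled. Until it is, what A and B encode is unknown. Once three labels are used, the figures fall to about 55% correct against 33% by chance, and 12% at 80% certainty or more with blocks 3/6/9.

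Fourth, there are safeguards: randomly varied block sizes, closed envelopes, a restricted list, allocation only just before stimulation, and eligibility screening by a trained clinician. They reduce the opportunity for selection. They do not stop earlier letters from being informative to someone who sees them.

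**Conclusion.** The point holds in conditional form. The stated choice of small blocks with one shared pair of letters makes about 70% of next letters guessable (69.5% to 71.4% over the size probabilities tried) against 50% by chance. About 28% to 57% are predictable with at least 80% certainty. This rests on a single two-letter list with all earlier letters visible to the person who enrols. Selection bias further requires that a letter be linked to a treatment, which one unblinding, the sham-only screen flicker or the fixed exposure could do.

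Two stronger readings should be avoided. One is that half of all allocations are predictable with at least 80% certainty: that is only the equal-probability case. The other is that larger three-arm blocks would cut this share from 52% to 8%: that comparison mixes the change in number of labels with the change in block size. With three arms throughout, the change is from 12% to 8%.

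**What to change.** In the Randomization section, replace the shared letter by a participant-specific device code in each envelope. This is the main remedy: past envelopes can no longer be counted, and unblinding one participant no longer exposes an arm. The sponsor should confirm that the device's study mode accepts individual codes, since the protocol does not say.

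In addition, drop the block of 2 and use varied block sizes that are multiples of three, for example 6, 9 and 12 at random. Do not disclose the sizes to recruiting or session staff; the current sizes are already in print. One sentence stating that those who enrol have no access to earlier allocations would settle the open condition.

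The cost is a new computer-generated list and relabelled envelopes, which is small if done before enrolment starts. The downside is slightly looser balance within blocks, negligible at 109 per group.
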